### Participants

A total of 40 women (20 subjects per arm) with breast cancer and stable osteolytic bone metastases in cervical, thoracic and/or lumbar vertebrae will be invited to participate. They will be included if they have not engaged in regular exercise in the past 3 months (defined as undertaking structured aerobic and/or resistance training two or more times per week). Due to the novelty of this explorative clinical trial, our sample size is based on previous preclinical animal studies [13, 70–72], human pilot studies [14, 56, 58, 73, 74] and consideration of the ability to recruit patients with advanced breast cancer and osteolytic bone metastases during the trial. Specifically, to achieve 80% power at an alpha level of 0.05 (two-tailed), 16 subjects per group are required to demonstrate a meaningful difference (effect size ≥ 1.0) at the completion of the study for the primary endpoint, and most secondary endpoints. To account for an attrition rate of up to 25%, 40 subjects will be randomised equally between the study arms (exercise, *n* = 20; control, *n* = 20).

Patients are permitted to receive radiotherapy for non-spinal bone metastases while enrolled in this trial. Patients require medical clearance prior to enrolment, therefore must achieve an Eastern Cooperative Oncology Group (ECOG) performance status ≤ 1, and must not have any acute illness, significant bone pain or cardiovascular or neurological disorders that could inhibit exercise participation as judged by their managing physician. All participants must provide written informed consent prior to participation. Patients will be excluded from this trial if they are receiving experimental treatments. The protocol has been approved by the Human Research Ethics Committee (HREC) of Edith Cowan University (ECU), Project ID 14266 [name]; St John of God Hospitals (SJOG), Project ID 969 and Sir Charles Gairdner and Osborne Park Health Group (SCGOPHG), Project ID 2016–118. This trial is also registered with the Australia and New Zealand Clinical Trails Register (ANZCTR), Trial ID ACTRN-1261600136842.

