## Methods

### Study design

This single-blinded (investigators blinded to group allocation), two-armed, randomised and controlled (supervised exercise versus usual medical care) explorative clinical trial will examine the feasibility, safety and preliminary efficacy of combining targeted spinal isometric training with modulatory, multi-modal exercise (M3EP-SIT) in women with advanced breast cancer and stable osteolytic spinal bone metastases. The exercise group (intervention arm) will receive an individually tailored and supervised 12-week exercise programme involving resistance, aerobic, flexibility and isometric exercises in addition to usual medical care. The control group will receive usual medical care only during this time and will be asked not to change their baseline levels of physical activity. However, following the trial, the control group will be offered the same exercise programme if proven to be safe and efficacious. This procedure has been shown to be an effective strategy to minimise study contamination, patient withdrawal or loss of patients to follow up in prior exercise oncology trials [14, 52, 64–68].

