#### Primary Endpoint

##### Feasibility

Study and programme feasibility will be quantified through a series of multi-item categories including patient recruitment and trial completion, patient safety and tolerance and program adherence and compliance (Table 2). Programme safety will be assessed by recording the incidence and severity (grading) of adverse events and/or skeletal complications [18] throughout the on-trial period for the intervention and control arms in accordance with the common terminology criteria for adverse events (CTCAE) v5.0 criteria. Skeletal complications will include heightened bone pain at sites of known bone metastases and/or pathological skeletal fractures. The nature, severity and impact of bone pain will be examined using the Functional Assessment of Chronic Illness Therapy (FACIT) bone pain questionnaire at baseline and post intervention.

**Table 2 Tab2:** Schedule of assessments at baseline and post intervention

Measures	Baseline	Post intervention
Tumour morphology (off-site)		
- MRI: T1-axial	X	X
Tumour biomarkers		
- Blood: HIF-1α, TGF-β	X	X
Anthropometry		
- Height (cm)	X	
- Weight (kg)	X	X
- Waist circumference (cm)	X	X
- Hip circumference (cm)	X	X
- Femoral length (mm)	X	
- Tibial length (mm)	X	
- Body mass index (kg/m^2^)	X	X
- Waist-to-hip ratio	X	X
Body composition		
- DXA: whole-body, spinal, hip	X	X
- pQCT: femoral, tibial	X	X
Physical assessments		
- NeuroCom Balance Test	X	X
- 1RM Strength Test (Leg Extension)	X	X
- 400 m Walk Test	X	X
- Timed Up and Go Test	X	X
Other biomarkers (off-site)		
- Blood: P1NP, ALP, CRP, fasting glucose and lipids	X	X
- Urine: NTx	X	X
Questionnaires		
- Demographic and health history	X	
- Concomitant medications	X	X
- Health-related quality of Life (SF-36)	X	X
- Cancer-specific quality of life (EORTC: QLQ30, BR23)	X	X
- Bone Pain (FACIT-BP)	X	X
- Brief Symptom Index (BSI-18)	X	X
- Insomnia Severity Index (ISI)	X	X
- Godin Leisure-time Exercise	X	X
Exercise programme		
- Clinic exercise record sheet (prescribed vs. actual)	At each exercise session	
- Home exercise record sheet (prescribed vs. actual)	At each exercise session	
- Pre-session bone pain, muscle soreness and fatigue (VAS)	At each exercise session	
- Post-session rating of perceived exertion and tolerance (VAS)	At each exercise session	

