*Abbreviations: HIF-1α* hypoxia-inducible factor 1-alpha, *TGF-β* transformation growth-like factor beta, *DXA* dual-energy x-ray absorptiometry, *pQCT* peripheral quantitative computed tomography, *P1NP* amino-terminal propeptide of type 1 procollagen, *NTx* amino-terminal collagen type-1 telopeptide, *ALP* alkaline phosphatase, *CRP* C-reactive protein, *SF-36* Short Form-36, *EORTC* European Organisation for Research and Treatment of Cancer, *FACIT-BP* Functional Assessment of Chronic Illness Therapy-Bone Pain, *VAS* visual analogue scale

Programme tolerance, adherence and compliance will be assessed in the intervention arm only. Specifically, programme tolerance will be quantified by routinely measuring pre-session bone pain, muscle soreness and general fatigue at each exercise session by visual analogue scale (VAS, 0–10) and by recording post-session rating of perceived exertion (Borg scale, 0–10) and post-session tolerance (VAS, 0–10) after each exercise session. Programme adherence and compliance will be assessed using an exercise diary completed by the patient at all clinic-based and home-based exercise sessions to record volume of resistance training (weight lifted (kilogrammes), sets and repetitions), aerobic training (intensity (level), duration (minutes), speed (revolutions per minute), heart rate (maximum and average) and rating of perceived exertion), flexibility training (repetitions and hold time (duration)) and isometric training (repetitions and hold time (duration)) completed. These data will be compared to the prescribed and individualised exercise programme provided to each patient in order to establish programme adherence (completed versus missed sessions) and compliance (prescribed versus actual exercise completed for each training mode (resistance, aerobic, flexibility and isometric)).

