### Dissemination plan

Demonstrating the feasibility and safety of delivering targeted exercise (controlled mechanical loads) to skeletal sites with osteolytic lesions in patients with advanced cancer will lead to potential changes in clinical practice. Accordingly, if proven to be safe and feasible, the outcomes of this pilot study will form the basis of future phase II and III clinical trials to establish efficacy; will be published in high-impact peer-reviewed journals; will be presented at national and international conferences or research meetings and will be delivered to the community, consumer-led forums, local hospital departments and university seminars. Evidence from this pilot study may contribute to the renewal of current clinical exercise oncology guidelines for patients with cancer, specifically those in the advanced stages with a high disease burden, within national and international exercise and oncology associations.

Last, the National Breast Cancer Foundation is a charitable organisation dedicated to improving patient outcomes for women and men with breast cancer. As the funder of this pilot study, the National Breast Cancer Foundation will assist with disseminating study outcomes through their extensive clinical, academic and consumer networks nationally. Similarly, the Cancer Council of Western Australia is the premier cancer charity in Western Australia, with wide-reaching connections to clinicians, academics, cancer survivors and their families, and will also assist in disseminating study outcomes through their state-wide networks.

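### The 80% power at an effect size of 1.0 is claimed for the primary endpoint, but that endpoint is multi-item feasibility and names no variable to which the calculation applies

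*Protocol article*

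**What the plan says.** The Participants section bases the sample size partly on earlier animal and pilot studies and on the ability to recruit. It then gives a formal calculation, "to achieve 80% power at an alpha level of 0.05 (two-tailed), 16 subjects per group are required". The purpose of that calculation is put as "to demonstrate a meaningful difference (effect size ≥ 1.0", and the section applies this "at the completion of the study for the primary endpoint, and most secondary endpoints". Allowance for loss follows: "To account for an attrition rate of up to 25%, 40 subjects will be randomised equally between the study arms", that is, 20 per arm.

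The Feasibility section, under Primary Endpoint, defines that endpoint: "Study and programme feasibility will be quantified through a series of multi-item categories", covering recruitment and completion, safety and tolerance, and adherence and compliance. It adds: "Programme tolerance, adherence and compliance will be assessed in the intervention arm only". Adverse events and skeletal complications are recorded by incidence and grade in both arms. The Abstract lists several primary endpoints and describes feasibility and safety as the principal aim.

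Two later steps depend on what the trial shows. Under Study design, "the control group will be offered the same exercise programme if proven to be safe and efficacious". Under Dissemination plan, "if proven to be safe and feasible, the outcomes of this pilot study will form the basis of future phase II and III" trials.

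**The concern.** A power statement needs a variable, a comparison and an effect on that variable's scale. An effect size of 1.0 with 16 per group is a comparison of two means on one continuous outcome measured in both arms. The primary endpoint, as the protocol defines it, contains no designated outcome of that kind.

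This matters because feasibility and safety are the main question. A reader who takes the Participants section at face value would treat a between-arm safety comparison with no significant difference as an 80%-powered result. The same reader would not see how wide the intervals around the feasibility proportions will be.

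**Working it through.** **1. Reproduce the plan's figure.** Inputs from Participants: two-sided alpha 0.05, power 80%, standardised difference d = 1.0, 1:1 allocation.

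- Normal approximation: n = 2(1.960 + 0.842)² / 1.0² = 15.7, so 16 per group. Power at 16 is Φ(√(16/2) − 1.960) = Φ(0.868) = 80.7%.
- Noncentral t: n = 16.7, so 17 per group. Power is 78.1% at 16.
- After the stated 25% attrition, 20 × 0.75 = 15 per arm remain. Power at d = 1.0 is then 75.3% (t) or 78.2% (normal). With no attrition, 20 per arm gives 86.9% (t).

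The 16 is therefore reproduced, as a comparison of two means.

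**2. Look for a primary variable it could apply to.** Table 1 has 20 distinct items:

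| Category | Items | Where measured | Type |
|---|---|---|---|
| Recruitment and completion | 9 | listed for the trial as a whole | counts, rates |
| Safety | 3 | both arms | event counts, grades |
| Tolerance | 4 | exercise arm only | session ratings |
| Adherence | 2 | exercise arm only | session counts |
| Compliance | 2 | exercise arm only | prescribed against actual, percent |

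The eight items in the last three rows have no control value, so no between-group d exists for them. The first nine are counts or rates. Completion and drop-out could be split by arm, but they would still be proportions. Only the three safety items are scheduled for both arms, and they are counts and grades.

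**3. What 20 per arm gives for between-arm safety.** The event rates are assumptions, because the document states none. Two-sided alpha is 0.05. The last column uses the uncorrected normal approximation as a stand-in for the Pearson chi-square test named under Statistical analysis.

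| Control vs exercise | Fisher exact | Normal approximation |
|---|---|---|
| 5% vs 15% | 7% | 18% |
| 5% vs 25% | 30% | 42% |
| 10% vs 20% | 7% | 14% |
| 10% vs 30% | 24% | 35% |
| 10% vs 50% | 74% | 81% |

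For 80% power by Fisher's test, exercise-arm incidence would have to reach about 45% against 5%, or 53% against 10%.

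**4. Precision (Clopper-Pearson, two-sided 95%; observed counts are illustrative).**

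- 0 events in 20 exercisers: upper limit 1 − 0.025^(1/20) = 16.8%. One event in 20: upper limit 24.9%.
- Chance of seeing no event in 20: 0.95^20 = 36% if the true rate is 5%; 0.90^20 = 12% if it is 10%.
- 16 of 20 adhering or completing (80%): 56% to 94%.
- 30 of 40 completing, which is the planned 25% attrition over the whole trial: 59% to 87%.

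**The case against.** The strongest reply is that one score measured in both arms does appear under the Primary Endpoint heading: the FACIT bone pain questionnaire, at baseline and after the intervention. A standardised difference could apply to it, so it would be too much to say that nothing under that heading can take a d. It does not rescue the sentence. The Abstract lists bone pain among the secondary endpoints, the questionnaire is described again among the secondary measures, and Participants does not name it.

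The trial also calls itself explorative, and the sample size rests partly on earlier studies and on recruitment. That stands. It makes a formal power claim unnecessary, but it does not make the claim correct.

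A reader might infer more than the document supports:

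- **That 16 is miscalculated.** It is right by the normal approximation and one short by the t test.
- **That the primary endpoint is mostly one-armed.** By item, 8 of 20 are; safety is recorded in both arms.
- **That safety can never be shown with this sample.** This depends on an acceptable rate, which the document does not give. No written rule declares safety from zero events, and the text does not tie its later decisions to the power calculation.
- **That missing numeric progression criteria are an error.** They may sit in a fuller protocol or analysis plan that is not shown.
- **That the safety limits should be computed on 15 completers.** Adverse events are recorded throughout the on-trial period, so women who leave also contribute.

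**Conclusion.** The concern holds as a misstatement of what the design delivers: the 80% power claimed for the primary endpoint has no variable to attach to. The calculation itself is sound for a continuous outcome measured in both arms, at 78% power for 16 per group and 75% for 15 by the t test, when d = 1.0.

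For the safety items, the only primary category scheduled by arm, Fisher power at 20 per arm is about 7% to 30% for the assumed differences of 10 to 20 percentage points shown above. For single-arm feasibility and safety proportions, the information is an interval: an upper limit near 17% after no events, or a span of nearly 40 percentage points around 80%. The event rates and observed counts are assumptions. The conclusion about the power sentence does not depend on them, because it follows from how the endpoint is defined.

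**What to change.** - In Participants, delete the reference to the primary endpoint from the power sentence. Attach the d ≥ 1.0 calculation to named continuous secondary outcomes measured in both arms. State its power by the t test: about 78% at 16 per group and about 75% at the 15 left after 25% attrition.
- Justify 20 per arm for feasibility and safety by precision, and commit to exact 95% confidence intervals, with the examples above as the expected widths.
- Where conclusions on safety and feasibility are described as proven, describe them as estimates with their intervals.
- The Abstract (Methods) and Study design make the control-arm offer depend on safety and efficacy. The Abstract (Discussion) and Dissemination plan make later use depend on safety and feasibility. These conditions govern different steps, but the efficacy assessed here is called preliminary, so the sponsor should reconcile the passages. This review does not propose which condition should apply.

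The cost is wording only. The number randomised, the measurements and the conduct stay as they are. The downside is that the trial can no longer say it is powered for its primary endpoint.

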### Randomisation

Patients will be randomly allocated in a ratio of 1:1 to the two study arms: exercise or usual care, stratified by age (≤ 60 years, > 60 years), hormone receptor (HR) status (HR+, HR-) [69] and time since completion of palliative radiotherapy to target spinal lesions (< 3 months, ≥ 3 months) and/or time since commencing or changing hormone therapy and/or chemotherapy (< 3 months, ≥ 3 months). A research officer with no patient contact will be responsible for randomisation of patients into either group using a computer-generated code through a random-assignment programme. Study investigators and exercise physiologists conducting testing procedures will be blinded to group allocation. Only exercise physiologists outside the research team will be permitted to deliver the exercise intervention to participants in order to maintain integrity of the blinding process.

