### Statistical analysis

Data will be analysed using SPSS (IBM Corporation; Chicago, IL, USA). Normality of distribution of continuous variables will be determined by Shapiro-Wilk test and visual inspection of the data. Analyses will include standard descriptive characteristics, the *t* test and two-way (group × time) repeated measures analysis of variance (ANOVA) (or analysis of covariance as appropriate) to examine differences between groups over time. Any data that are not normally distributed will be log-transformed or non-parametric tests will be used. The Pearson chi-square test will be used to analyse categorical variables. An alpha level of *p* ≤ 0.05 will be applied to establish statistical significance. Effect sizes will also be calculated in accordance with Hopkins [90]: *d* ≥ 0.2 is small; *d* ≥ 0.6 is moderate; *d* ≥ 1.2 is large; *d* ≥ 2.0 is very large. Incomplete data and missing values will be primarily managed using an intention-to-treat approach [91] with multiple imputation, specifically using maximum likelihood imputation of missing values. To ensure the robustness of our findings, a secondary sensitivity analysis [92, 93] will be conducted using a complete-cases approach.

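### Randomising 20 per arm does not cover 25% attrition: 15 per arm remain, one short of the 16 the plan requires for 80% power

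*Protocol article*

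**What the plan says.** The sample-size statement is in the Participants section of the protocol article. The goal there is 80% power with a two-sided 5% test, and the number needed for it is given as: "16 subjects per group are required to demonstrate a meaningful difference (effect size ≥ 1.0) at the completion of the study". The 16 is therefore a number of completers, not a number randomised. The claim is made for the primary endpoint and most secondary endpoints.

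The next sentence gives the allowance for loss: "To account for an attrition rate of up to 25%, 40 subjects will be randomised equally between the study arms", which is 20 in each arm. The same section opens with the same total, and the Randomisation section confirms 1:1 allocation. No other section gives a different sample size or attrition rate.

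The Statistical analysis section lists, for group comparisons, "the *t* test and two-way (group × time) repeated measures analysis of variance (ANOVA) (or analysis of covariance as appropriate"). Missing values are to be handled mainly by intention-to-treat with multiple imputation, with a complete-case analysis as sensitivity analysis.

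**The concern.** Three numbers are fixed: 16 completers per group, up to 25% attrition, and 20 randomised per arm. Any two determine the third, and the printed third does not match. A quarter of 20 is 5, so 15 remain.

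The likely slip is a common one: adding 25% of the required number instead of dividing by the fraction expected to remain. If so, the allowance printed as 25% is really an allowance of 20%.

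What is at stake is the power claim. At the attrition the plan says it covers, the trial falls below 80%, and readers of the secondary results would credit it with more power than it has.

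**Working it through.** **Inputs** (Participants and Randomisation sections): power 80%; alpha 0.05 two-sided; standardised effect d = 1.0, the lower end of the stated range; 16 per group required at completion; attrition up to 25%; 40 randomised 1:1, so 20 per arm.

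**1. Reproducing the 16.** The normal-approximation formula for two means is

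n per group = 2 × (1.960 + 0.842)² / d² = 2 × (2.802)² / 1 = 15.7, rounded up to 16.

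This matches the plan exactly.

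**2. Reproducing the 20.** 16 × (1 + 0.25) = 20 per arm, 40 in total. This matches too, but it is not the right inflation for a 25% loss. The article does not show its formula, so this route is an inference.

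**3. What 20 per arm leaves.** 20 × (1 − 0.25) = 15 per arm, 30 in total, against 16 and 32 required.

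**4. What 25% attrition needs.** 16 / (1 − 0.25) = 21.3, so 22 per arm, 44 in total (43 if the total is rounded instead: 32 / 0.75 = 42.7).

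**5. What 20 per arm can absorb.** 1 − 16/20 = 20%.

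**6. Power at d = 1.0, two-sided 5%:**

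| Completers per arm | Normal approximation | Two-sample t test (noncentral t) |
|---|---|---|
| 15 | 78.2% | 75.3% |
| 16 | 80.7% | 78.1% |
| 17 | 83.0% | 80.7% |

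At 15 per arm, power is below 80% in both columns. The effect detectable with 80% power by the t test is then d = 1.06. If the 30 completers split unevenly, t-test power is slightly lower: 75.1% for 14 and 16, 74.5% for 13 and 17.

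**7. A secondary remark on the 16.** For a two-sample t test the exact requirement is 16.7, so 17 per group. From 17, 20 per arm absorbs 1 − 17/20 = 15% attrition, and a 25% allowance needs 17 / 0.75 = 22.7, so 23 per arm (46). This is a one-patient difference from a usual planning approximation, and the finding does not depend on it.

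**8. Would baseline adjustment close the gap?** The article gives no correlation r between baseline and week 13, so the range below is assumed. With 15 per arm and d = 1.0 in units of the outcome SD, the effective d is 1/√(1 − r²) for ANCOVA and 1/√(2(1 − r)) for a change-score comparison. With two time points, the latter is equivalent to the group × time test.

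| Assumed r | ANCOVA power | Change-score (group × time) power |
|---|---|---|
| 0.3 | 79% | 61% |
| 0.5 | 86% | 75% |

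ANCOVA can recover the loss if the correlation is high enough. The group × time test does not do so at these values.

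**The case against.** The strongest case on the other side accepts the arithmetic and disputes its weight.

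- **25% is only an upper limit.** At 20% attrition or less the 16 is met. That is true, but the sentence claims to cover loss up to 25%, and between 20% and 25% it does not.
- **The gap is small.** It is one patient per arm. On the formula that yields 16, power drops to 78.2%, which is 1.8 points short. The larger figure of 75.3% combines two things: the lost patient (about 2.8 points on the t scale, 78.1% to 75.3%) and the move from the normal approximation to the t distribution. This stands, and both figures should be reported.
- **The t test is one of several listed analyses.** The article does not name it as the main one, nor say which test or standardisation the effect size of 1.0 refers to. This stands: the t-test powers are conditional on that reading. The shortfall of 15 against 16 is not.
- **Multiple imputation keeps all 40 patients.** It keeps them in the analysis set but does not by itself restore the information in unobserved week-13 outcomes. The plan inflates for attrition, so it treats dropouts as a loss of power.
- **This is a pilot.** The primary endpoint is multi-item feasibility, part of it measured in the exercise arm only, and a two-group power figure can hardly govern that. The efficacy results are preliminary. This limits the consequence, but the article does make a formal power claim and plans tests at the 5% level.

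None of this makes the three printed figures consistent.

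**Conclusion.** The statement is wrong as written. On the plan's own inputs, 25% attrition leaves 15 per arm where 16 are required, and 20 per arm supports an allowance of 20%, not 25%. That conclusion needs no assumption beyond equal loss in the two arms.

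Power at the stated limit is 78.2% (normal approximation) or 75.3% (t test) in place of 80%, a deficit of 1.8 to 4.7 points. This assumes a true effect of exactly 1.0, an unadjusted comparison of two means, and no information recovered for dropouts. A baseline-adjusted analysis could do better, by an amount that depends on a correlation the article does not give.

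The practical effect is modest. It bears mainly on the continuous secondary endpoints and does not threaten the feasibility and safety aims.

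**What to change.** Keep 40 patients, since the article says recruitment capacity helped set that number, and correct the sentence. Suggested wording:

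> With 20 patients per arm, 16 per arm are retained for attrition of up to 20%. At 25% attrition (15 per arm), power of a two-sample t test is about 75% for an effect size of 1.0, and 80% for an effect size of 1.06.

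If the sponsor prefers to stay with the normal approximation behind the 16, the power figure at 25% attrition is about 78%; the text should say which method is used. If the final model is a baseline-adjusted ANCOVA, its power can be quoted instead, with the assumed correlation stated (15 per arm: about 79% at 0.3, 86% at 0.5). Those figures should not be used for the group × time test.

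The alternative is to keep the 25% allowance and randomise 44 (22 per arm), or 46 starting from 17 per group. For a pilot limited by recruitment, this seems unnecessary.

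The cost of the preferred change is one sentence and a slightly less favourable stated figure, with no added patients and no change to the design.

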#### Secondary endpoints

##### Tumour morphology

Location of metastatic lesions will be initially identified through bone scans provided by the managing oncologist prior to referral to this study. Tumour morphology will be measured using axial T1-weighted magnetic resonance imaging (MRI) (1.5 T, Magnetom Essenza, Siemens, Victoria, Australia) in locations where osteolytic lesions have been identified in patients with bone metastases at either thoracic or lumbar spinal regions [75–78]. All patients will be scanned by the same radiologist using the same MRI machine and a standardised sequence and routine for scout and primary scan acquisition. Specifically, spinal bone metastases will be identified and confirmed using three preliminary axial scout scans in the sagittal plane to view the cervical, thoracic and lumbar regions, respectively (T2-weighted; imaging frequency = 63.66 Hz; slice thickness = 3.0–4.0 mm; spacing between slices = 3.6–6.0 mm; echo train length = 16–21; flip angle = 140–150°; acquisition matrix = 256\0\0\192 (cervical), 448\0\0\358 (thoracic) and 320\0\0\320 (lumbar)).

Primary scans of each affected vertebra will be performed in the transverse plane, capturing the vertebrae above and below to produce an image with three vertebrae in total (T1-weighted; imaging frequency = 63.66 Hz; slice thickness = 4.0 mm; space between slices = 4.2 mm; echo train length = 3; flip angle = 150°; acquisition matrix = 384\0\0\307). Following the acquisition of images, tumour morphology (volume (cubic millimetres) and intensity (watts per steradian (W/sr))) will be examined for each slice using ITK-Snap (V3.6.0) image analysis software [79] (Fig. 2). All images will be examined at the conclusion of the study by two independent researchers for consistency in analysis and to establish intra-rater and inter-rater reliability coefficients.

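### Tumour volume: imputation and the complete-case check both treat losses from death or spinal progression as unrelated to tumour growth, so the stated sensitivity analysis cannot reveal the resulting attenuation

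*Protocol article*

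**What the plan says.** **Endpoint.** Aim 2 (Background) is to explore whether the programme slows tumour growth in target osteolytic spinal lesions. The Tumour morphology section makes this a secondary endpoint: "Following the acquisition of images, tumour morphology (volume (cubic millimetres) and intensity" are to be examined slice by slice. Measurements and Table 2 place the MRI at baseline and post-intervention (weeks 0 and 13), with none in between.

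**Missing data.** Statistical analysis sets one approach for all incomplete data: intention-to-treat with multiple imputation, "specifically using maximum likelihood imputation of missing values". One sensitivity analysis, on complete cases, is offered to show that the findings are robust.

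**Losses and treatment on trial.** Participants allows for losses: "To account for an attrition rate of up to 25%, 40 subjects will be randomised equally between the study arms". The same section says "Patients are permitted to receive radiotherapy for non-spinal bone metastases while enrolled in this trial". Randomisation uses earlier radiotherapy to target spinal lesions as a stratification factor. The article does not say how spinal radiotherapy given during the 12 weeks affects the tumour endpoint.

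**Other recording.** Withdrawals, drop-outs, adverse events and skeletal complications are captured under feasibility and safety (Table 1 and Primary Endpoint). Skeletal complications are described as heightened bone pain at known metastases and pathological fracture. Spinal progression and spinal radiotherapy are not named.

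**The concern.** For most endpoints a missing week-13 value is a nuisance. For tumour volume it can be the outcome itself: a patient may have no week-13 scan because her spinal disease progressed. With no interim MRI, her growth leaves no trace in the volume data. Imputation under the usual assumption fills in what similar patients who stayed would have shown, and complete cases drops her. For a patient who has died, the imputed volume describes nothing real.

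The two analyses share the assumption that loss is unrelated to tumour growth once the recorded data are accounted for. Their agreement would look like robustness but would say nothing about this risk. If the programme changes how often patients are lost to spinal progression, in either direction, the tumour-volume comparison understates the change. That matters because the spinal isometric component is designed to load the lesion sites directly, and the results are meant to support phase II and III trials.

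**Working it through.** **1. The plan's own figures.** Inputs (Participants): two-sided alpha 0.05, power 80%, effect size 1.0.

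n per group = 2(z0.975 + z0.80)²/d² = 2(1.960 + 0.842)²/1² = 15.7, so 16. This matches the article.

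Attrition of 25% of 20 is 5 per arm, or 10 of 40 without an observed week-13 volume. That leaves 15 per arm, with power 78.2% at d = 1.0 (normal approximation). The article does not say how many of these losses would be due to progression.

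**2. What the two methods estimate.** The following are assumptions, because the documents give no progression rate:
- p = proportion of an arm with spinal progression
- δ = extra volume in progressors
- s = share of progressors scanned at week 13, the same in both arms
- all non-progressors are scanned, and exercise has no effect among them

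True difference (exercise minus control) = δ(pE − pC).

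Share of progressors among those scanned: q = sp/(1 − p + sp).

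Complete cases estimate δ(qE − qC). Imputation from baseline and arm has the same target, because it fills gaps with what scanned patients in that arm show.

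Worked case, 25% control v 10% exercise, s = ½, δ = 1 SD: qC = 0.125/0.875 = 0.143; qE = 0.05/0.95 = 0.053; estimate 0.053 − 0.143 = −0.09, against a true 0.10 − 0.25 = −0.15.

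| Progression, control / exercise | δ | True | Estimate, s = 0 | Estimate, s = ½ |
|---|---|---|---|---|
| 25% / 10% | 1 SD | −0.15 | 0 | −0.09 |
| 25% / 10% | 2 SD | −0.30 | 0 | −0.18 |
| 10% / 25% | 1 SD | +0.15 | 0 | +0.09 |
| 10% / 25% | 2 SD | +0.30 | 0 | +0.18 |
| 25% / 5% | 0.7 (log volume) | −0.14 | 0 | −0.08 |
| 25% / 25% | 2 SD | 0 | 0 | 0 |

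For the fifth row at s = ½: qE = 0.025/0.975 = 0.026, and 0.7 × (0.026 − 0.143) = −0.08.

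**3. Simulation of s = 0.** With 20 per arm, 4,000 runs, baseline-to-week-13 correlation 0.7 and a baseline-adjusted comparison, the mean differences were:

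| Progression, control / exercise | δ | All patients | Scanned only |
|---|---|---|---|
| 25% / 10% | 1 SD | −0.154 | −0.002 |
| 25% / 10% | 2 SD | −0.299 | −0.002 |
| 10% / 25% | 1 SD | +0.144 | −0.004 |
| 10% / 25% | 2 SD | +0.294 | −0.004 |
| 25% / 25% | 2 SD | −0.004 | −0.005 |

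**4. Would a worst-rank check see anything?** A separate simulation on the log-volume scale used SD of change 0.3, δ = 0.7, 25% v 5%, and all progressors unscanned. Multiple imputation and complete cases both gave 0.00 and rejected in about 4% to 5% of runs, which is the nominal level. Ranking progressors worst rejected in 19%.

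The benchmark is a trial with every patient scanned. Variance of change = 0.3² + 0.7²p(1 − p), which is 0.182 in controls and 0.113 in exercisers. SE = √((0.182 + 0.113)/20) = 0.121; 0.14/0.121 = 1.15; power ≈ Φ(1.15 − 1.96) = 21%. The ranked check recovers roughly what full data would offer, which is itself little. With equal progression of 15% its rejection rate was about 3% to 5%.

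**The case against.** **The effect may be small.** Tumour morphology is one of many secondary endpoints in a 40-patient pilot aimed mainly at feasibility and safety. Entry requires stable lesions and ECOG status of 1 or below, and follow-up is 12 weeks. A trial sized for an effect of 1.0 could not reliably detect differences of this order under any analysis. All of this stands and limits the weight of the point.

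**The detail may sit elsewhere.** Imputation variables and not-at-random analyses are commonly left to a full protocol or SAP. That stands for the imputation model. It does not remove the point, because the article itself names the missing-data method and the one check on it. Auxiliary data would help only unevenly: pre-session bone pain is recorded in the exercise arm only, and the FACIT bone pain questionnaire is given only at baseline and post intervention.

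**Stronger readings that the article does not support:**
- A reader might infer that only non-spinal radiotherapy is allowed, so that patients given spinal radiotherapy are set to missing and imputed. The sentence in Participants permits one thing and does not state the rest. Under intention-to-treat such a patient could still be scanned. Her volume is then observed but may be altered by treatment, which is a separate problem. Keeping such scans is a recognised treatment-policy choice.
- A reader might infer that progression is removed from the tumour result altogether. Patients who progress and are scanned still count. The zero estimates follow from assuming that none is scanned.
- A reader might infer that harm from loading lesions would be hidden. Adverse events, skeletal complications and withdrawals are recorded by other routes; only the tumour-volume result is affected.

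**Worst rank has its own bias.** Without an interim scan, progression would be detected clinically. Safety is recorded at each exercise session in one arm and on a tri-weekly record in the other, so ranking could penalise the more closely watched arm. This is a good reason not to make it the main analysis.

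**Conclusion.** The concern holds in a limited form. For patients with no week-13 scan because of death or spinal progression, both planned analyses assume that the loss is unrelated to tumour growth. A between-arm difference in such losses is therefore attenuated in the tumour-volume result, whether it reflects benefit or harm, and the complete-case check cannot reveal this.

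The size is unknown. Under the assumed rates of 25% and 10%, the tumour result loses all of a 0.15 to 0.30 SD difference if no progressor is scanned and about 40% of it if half are. With equal progression and equal scanning in the two arms, nothing is lost. These figures rest on assumed progression rates and shifts, no exercise effect among non-progressors, and an imputation model using baseline and arm. The point concerns a secondary endpoint and does not touch the primary feasibility and safety assessment.

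**What to change.** In Statistical analysis, for tumour volume:

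1. Keep the planned primary analysis.
2. Record the reason for each missing week-13 scan and for each scan taken after local treatment of a target lesion, and report the counts by arm beside the tumour result.
3. Beside complete cases, add a not-at-random sensitivity analysis. Rank patients with no week-13 scan because of death or spinal progression worst in a between-group comparison of volume change, or impute them with a stated range of unfavourable shifts (delta adjustment). In the ranked version, and in that sensitivity analysis only, also rank worst those scanned after local treatment of a target lesion.
4. Leave imputation in place for scans missing for unrelated reasons.

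The cost is one extra analysis and a reason recorded for each affected scan. A rank result is not in cubic millimetres. Progression would be detected clinically under surveillance that differs by arm, so the result should be read as a sensitivity analysis and not as the main tumour finding. No clinical rule changes.
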